men 18 years old and above have been conducted (as well as more than 650 no-flip procedures in children), suggest that the no-flip method is faster and easier and has no serious problems during or post-circumcision (Yan et al., 2010). Spontaneous detachment of the Shang Ring may be more likely following the no-flip technique compared to following the standard Shang Ring technique. A video of the no-flip technique can be watched at: <http://www.youtube.com/watch?v=MjJlQgU4HDw>.

Another potential innovation that could significantly improve the treatment paradigm for Shang Ring MC is the replacement of injectable local anesthetics with topical agents. Injected anesthesia, the current standard for Shang Ring circumcision, requires a skilled provider and is the most painful part of the procedure. Some men who fear needles may avoid circumcision, and use of a topical anesthetic would potentially improve acceptability of MC. Additionally, hypodermic needles can pose a risk to the provider. Reuse of needles and syringes is a potential source of infectious transmission, and safe disposal of needles and syringes can be problematic. Therefore, identifying an effective topical agent would significantly improve the treatment paradigm for Shang Ring MC and alleviate needle disposal concerns. In addition to being easier, topical anesthesia will likely be better tolerated when the faster no-flip technique is used.

Topical anesthesia is used with another male circumcision device, PrePex (Bitega et al., 2011, Mutabazi et al., 2012, Galukande et al., 2014). Although the mechanism of action of the PrePex Device is different, it does provide a theoretical basis for use of topical anesthesia with MC devices. Indeed, recently another new MC device, named the Unicirc was introduced with a mechanism of action is similar to the Shang Ring using topical anesthesia (see video at <https://www.youtube.com/watch?v=e3i1MlhV1ZU>). Additionally, there are some preliminary promising results from use of topical anesthesia in men and boys in China (personal communication). With application of topical anesthetic cream to the mucosal layer of the foreskin and dwell times of 15-45 minutes, adequate anesthesia to carry out circumcision is achieved. While data from China are limited and preliminary, they suggest that topical anesthesia for Shang Ring MC is worth pursuing more systematically.

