### 3.2 Phase II

#### 3.2.1 Primary Endpoints

- The outcome metric for the primary outcome will be maximum pain reported to have been experienced by participants during the Shang Ring circumcision, assessed using the visual analogue scale (VAS), reported immediately after completion of the Shang Ring circumcision procedure

---

i AEs will be defined in the study manual of operations and will be based on those found in the report of the January 2013 meeting of the WHO Technical Advisory Group on Innovations in Male Circumcision, as well as those being used in ongoing pilot implementation studies of PrePex, another male circumcision device being studied in Africa.

ii Complete clinical wound healing is defined as intact epithelium (unbroken skin) covering the wound as judged by the provider on visual inspection, meaning that none of the following are present: scabbing, drainage, moisture, gaps between epithelial edges or ulceration.

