### **Phase II**

Assuming positive outcomes of Phase I, we will use the no-flip technique for all Shang Ring circumcisions in Phase II.iv In this phase, participants will be randomized to topical or injectable anesthesia in a 2:1 ratio. We rationalize the 2:1 randomization scheme given that we will have just completed Phase I in which 230 men and boys will have been circumcised using the no-flip technique with injected anesthesia. However, given the subjectivity associated with using reported pain as the primary endpoint, we believe it is critical to randomize participants in this phase of the study. Because of the possibility that boys and men could respond differently to use of topical anesthesia we will recruit participants equally in two age groups; 50% ages 10-15 years old and 50% those over 15 years old.

To get a better sense of minimum dwell time necessary for adequate anesthesia, we will test for anesthetic effect more frequently (e.g. every 3-5 minutes) in the first 10 participants randomized to the topical arm in each age group (10-15 and over 15 years old), as well as any participants randomized to the injectable arm during this period. During this time we will also closely monitor the occurrence of any significant problems with application of the topical anesthesia or potency of the anesthesia with the topical agent. This will allow us to establish a minimum dwell time which will be important for logistic and program planning purposes, although each participant will be tested for numbness as described below before the circumcision procedure is started. Given the previous experience with use of EMLA cream for male circumcision, we are expecting that it will provide adequate anesthesia for Shang Ring circumcision. Should we determine that in fact it does not, or that there are unexpected problems, we may explore other options such as 4% or 5% lidocaine cream.

---

iv Given the experience with the no-flip technique in China and our experience with the technique in the pilot study on use of the Shang Ring in children in Kenya, we are not expecting any outcomes that might suggest that the no-flip technique is inappropriate, however, should that be the case, we will use the standard Shang Ring technique for circumcisions in Phase II.

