The injectable approach shall utilize a combination of a penile and a ring block with 1% lidocaine injected with a small gauge needle. This is the standard anesthesia approach used in the Kenya VMMC program. The maximum amount of lidocaine administered will be 4.5 mg/kg. Onset of action typically requires 3 to 10 minutes. The topical approach shall consist of applying EMLA cream to the both the inside and outside surfaces of the foreskin. The anesthetic will then be allowed to dwell for up to 45 minutes for onset of action, with appropriate adjustments made based on the run-in described in the previous paragraph.

In both the injectable and topical anesthetic groups, we will test for numbness using the approach that is currently used, i.e. using blunt forceps on all of the quadrants of the penile shaft, on both the cutaneous and the mucosal sides to determine if anesthesia has taken effect. If it is determined that anesthesia has not taken effect in any participant in the topical group, we will resort to injectable anesthesia.

The Wong-Baker FACES Visual Analogue Scale (VAS) shall be used for pain assessment as we have done in our previous Shang Ring studies (Barone et al., 2011; Barone et al., 2012; Barone et al., 2013, Sokal et al., 2014).

The immediate complications of the circumcision procedure will be recorded on either an Adverse Event (AE) or Serious Adverse Event (SAE) form and may include such findings as: excessive pain, excessive bleeding, anesthetic-related complications, excessive swelling, excessive skin removal, and damage to the penis (e.g. injury to the glans or urethra). Data on procedure times and surgical difficulties, including problems with use of Shang Ring shall also be collected.

Participants will be instructed to return to the study site if they experience medical events such as severe discoloration of the penis, signs of infection (purulence), severe or increasing pain, or any other significant concern that they may have.

Study staff will contact participants or their parents/LAR if appropriate by mobile phone call and/or SMS to remind them of their next follow-up visit. All reasonable efforts will be made to contact those who do not return for follow-up visits. If necessary home visits may be resorted to especially in the case where the ring has not yet been confirmed at the site to have been removed or the client has an AE.

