### 9.2 Analysis Plan Summary

A detailed analysis plan that covers both the final analysis and the planned interim analyses will be developed and reviewed and approved internally prior to initiation of the analysis. The following is a summary of the planned analyses for the two phases. Any deviations to be made from this summary plan will be documented in the detailed analysis plan.

In Phase I, the frequency and percentage of men with procedure-related AEs will be tabulated by severity, both overall and by site. Listings of AEs will include information on duration, outcome, severity, and relation to study procedures. Listings of any serious adverse events will also be provided. Shang Ring circumcision and removal procedure data (e.g. time of circumcision and removal, problems encountered, ring sizes used) will be descriptively summarized. Data on operative and post-operative pain, time to return to normal activity, participants' opinions of the Shang Ring procedure and participants' satisfaction with the post-circumcision cosmetic results will be descriptively summarized. Time to complete wound healing will be evaluated using a Kaplan–Meier estimator.

As Phase II is a randomized study of acceptability and safety, primary analyses will be conducted using an as-treated approach (i.e., depending on anesthesia method actually received). However, any deviations between the as-treated approach and a strict intention-to-treat approach will be presented to allow for the assessment of potential biases. Some secondary analyses on safety endpoints may be repeated using an intention-to-treat approach, as relevant.

VAS pain scores will be compared between randomization groups to estimate the efficacy of anesthetic technique at the time of surgery. The frequency and percentage of men with AEs will be tabulated by randomization group, relation to study procedures, and by severity, both pooled across sites and separately within each site. The analysis of AEs will include information on duration, outcome, and relation to study procedures. Stratification by severity will also be considered.

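### The Phase II pain comparison is read as anesthetic efficacy, but it is taken after topical participants who are not numb have been injected, so it cannot show whether the cream replaces the needle

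*Combined protocol and SAP*

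**What the plan says.** The Phase II primary endpoint (section 3.2.1) is the "maximum pain reported to have been experienced by participants during the Shang Ring circumcision", reported straight after the procedure. Section 9.2 gives its use: "VAS pain scores will be compared between randomization groups to estimate the efficacy of anesthetic technique at the time of surgery".

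Section 8.2 (Phase II) puts a test before the procedure: "each participant will be tested for numbness as described below before the circumcision procedure is started". For topical participants who do not pass it: "If it is determined that anesthesia has not taken effect in any participant in the topical group, we will resort to injectable anesthesia". Both arms are tested, but no matching step is written for an injectable participant who is not numb.

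On the analysis set, section 9.2 says "primary analyses will be conducted using an as-treated approach (i.e., depending on anesthesia method actually received", and adds that "any deviations between the as-treated approach and a strict intention-to-treat approach will be presented to allow for the assessment of potential biases". It does not say how to classify a participant who received both cream and injection.

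The purpose in section 1.2 is the "replacement of injectable local anesthetics with topical agents". Section 3.2.2 lists dwell time, potency and problems as secondary endpoints. It does not name the proportion of topical participants who reach numbness without an injection.

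**The concern.** The replacement question turns on two quantities: how much it hurts when the cream works, and how often the cream works without a needle. The pain score carries the first only in diluted form and the second not at all, because a failure of the cream is converted into an injection before the score is taken. Section 9.2 still treats the score as the measure of the technique's efficacy.

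If rescue is common, the randomised groups can show similar pain because many in the topical arm were injected. The trial could then report a pain result with no defined way to say whether it supports dropping the needle. The power statement in 9.1 makes no allowance for this dilution.

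**Working it through.** **Inputs.** From section 9.1: 345 randomised 2:1, so 345 × 2/3 = 230 topical and 115 injectable; at least 300 with complete follow-up, so 200 and 100; difference 1 on a 0 to 10 scale; SD 1.8; two-sided 0.05; stated power 100%. Section 9.1 calls the scores postoperative; I take them to be the primary pain score. Because that score is recorded on Day 0, 230/115 is the more relevant pair. The rescue rate f is not in the documents, so the full range is shown.

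**Plan's own figure.** SE = 1.8 × √(1/115 + 1/230) = 0.2056. Power = Φ(1/0.2056 − 1.96) = Φ(2.90) = 99.8%. At 200/100, SE = 0.2205 and power is 99.5%. The stated 100% is reproduced to rounding, with no rescue.

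**Effect of rescue on the randomised comparison.** Assume that rescued participants report pain like injected ones on average. Then:

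- topical arm mean = (1−f) × (cream-numbed mean) + f × (injected mean)
- expected difference = (1−f)D
- topical arm variance = 1.8² + f(1−f)D²
- SE = √(1.8²/n_inj + [1.8² + f(1−f)D²]/n_top)

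Example at f = 0.5, D = 1, 230/115: the variance is 3.24 + 0.25 = 3.49, SE = √(3.24/115 + 3.49/230) = 0.2082, and power = Φ(0.5/0.2082 − 1.96) = Φ(0.44) = 67%.

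| Rescued (f) | Expected difference, D = 1 | Power, 230/115 | Power, 200/100 |
|---|---|---|---|
| 0% | 1.00 | 99.8% | 99.5% |
| 10% | 0.90 | 99.2% | 98.2% |
| 25% | 0.75 | 95.1% | 92.1% |
| 50% | 0.50 | 67.1% | 61.0% |
| 75% | 0.25 | 22.6% | 20.2% |
| 100% | 0.00 | 5% (alpha) | 5% (alpha) |

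With D = −1 the differences change sign and the power figures are the same. For a given D, rescue shrinks an advantage of the cream just as it shrinks a disadvantage.

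**As-treated comparison.** If rescued participants are counted as injected, the topical group keeps only those in whom the cream worked, and the injectable group gains the cream failures. If failing the numbness test is unrelated to later pain, the expected difference stays at D but rests on fewer topical participants. If it is related, the comparison is selected. In a simulation with an assumed correlation of 0.5, a no-rescue difference of 2 and 50% failure, the as-treated difference was 1.28, with 115 of 230 topical participants left. If participants who received both were instead counted as topical, the as-treated and randomised sets would coincide for these people. The plan does not say which applies.

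**The case against.** **Pain is the stated objective.** Section 2.2.1 asks about pain during the procedure, and cream first with injection if not numb is a legitimate strategy to evaluate. This stands: the randomised comparison is valid for that strategy. It does not by itself measure the cream or answer the replacement question.

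**Failure would be seen.** Section 8.2 tests the first 10 topical participants in each age group more often and allows another agent if the cream proves inadequate. Section 9.3 has a monitoring review after 40 topical participants per age group. Section 9.2 promises to present departures from intention to treat. So a wholly ineffective cream would be unlikely to go unnoticed. Partial failure is the realistic case. No threshold for inadequacy is given, the proportion numbed by cream alone is not named among the interim data, and no efficacy conclusion is tied to it.

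**Stronger readings are not supported.**

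- A reader might infer that more frequent failure makes topical look better. That needs cream-numbed pain above injection pain. Section 1.2 calls the injection the most painful part of the procedure, and section 3.2.1 does not say whether that pain counts in the score, so D could be negative. Failure would then erode an advantage. If a weaker cream both fails more often and hurts more, the randomised difference need not move in one direction.
- A reader might infer that an inert cream would score the same as the injection. That follows only for the randomised comparison. As treated, with rescued participants counted as injected, no topical group would remain.
- A reader might infer that a non-significant difference would be declared equal pain. The plan states no margin and no such rule; it speaks of estimation.

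**Conclusion.** The point holds in this form. As randomised, the Phase II pain comparison estimates cream first, injection if not numb, and not the efficacy of the cream. The quantity that decides replacement, the proportion numbed without a needle, is not a defined outcome. Section 9.2 also points to two different analysis sets for the same comparison, and the as-treated one would select cream responders and give up the randomisation.

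The loss is modest at low rescue rates (power about 99% at 10%) and serious at high ones (67% at 50%, 23% at 75%, with 230/115). These figures rest on D = 1, SD 1.8, rescued participants scoring like injected ones, and cream-numbed pain that does not change with f. The documents give no rescue rate, so which row applies is unknown. They do not support a claim about the direction in which failure would favour either arm.

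**What to change.** 1. In section 9.2, reconcile the two statements on the analysis set. Name the randomised comparison as primary for the pain score and state that rescued topical participants stay in the topical arm. Any as-treated result is then supportive, with a stated rule for participants who received both.
2. Report the proportion of topical-randomised participants numbed without injection, with an exact 95% CI, overall and by age group, as a key outcome. State that it is read together with the pain score before any efficacy or replacement claim. For scale, 180 of 200 gives 90% (85.0% to 93.8%) and 150 of 200 gives 75% (68.4% to 80.8%). A formal co-primary endpoint is not needed; without a success threshold it would decide nothing.
3. Add a sensitivity analysis that ranks rescued topical participants worse than all non-rescued participants and compares the arms with a rank test stratified by age group.
4. In section 9.1, state that the 100% power assumes no rescue, and show power over a range of rescue rates.

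The rescue procedure itself is unchanged. No extra participants are needed, and section 13.1 already has anesthetic details collected on Day 0; the team should confirm that the form separates cream alone from cream plus injection. The detailed analysis plan is still to be written, so most of this can go there. The protocol wording needs executive committee and ethics approval under section 11.0. The downside is that the conclusion on topical anesthesia may become less favourable.

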#### **2.2.2 Secondary Objectives**

- Compare safety of topical vs. injectable anesthesia for local anesthesia during Shang Ring circumcision
- Compare ease of use of topical vs. injectable anesthesia for local anesthesia during Shang Ring circumcision
- Explore service optimization for use of topical anesthesia in conjunction with Shang Ring circumcision
- Compare duration of post-procedural analgesic effects between the topical vs. injectable anesthesia groups
- Compare satisfaction with the topical vs. injectable anesthetic among study participants

- Compare satisfaction with the topical vs. injectable anesthetic among circumcision providers

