### 3.2.2 Secondary Endpoints

- To compare safety of the two anesthetic techniques we will document rates of moderate and severe AEs, device-related malfunctions, occurrence of device displacement, and time to complete clinical wound healing
- To compare ease of use of the topical vs. standard injection technique for local anesthesia during Shang Ring circumcision, we will document dwell time required for onset of adequate anesthesia with the topical cream and time to adequate anesthesia with injectable anesthesia, potency of anesthesia provided by both techniques, and problems encountered during anesthesia with the two techniques.
- We will also explore service optimization in terms of determining how to best sequence and group patients for Shang Ring circumcision given the dwell time necessary for topical anesthetic effect.
- To compare duration of post-procedural analgesic effects between the topical vs. injectable anesthesia groups, we will document reported pain at various time points such as 1 and 24 hours post-circumcision between the two groups using the VAS.
- To compare satisfaction with topical vs. injectable anesthetic, we will interview study participants and their parents or legally acceptable representative (LAR) as appropriate to document acceptability and satisfaction with the circumcision, the Shang Ring procedure, post-procedure pain, and time to return to normal activity between the two techniques
- To compare satisfaction with the topical vs. injectable anesthetic among clinical providers in the study, we will interview them about their experiences, acceptability and satisfaction with the two anesthetic techniques

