## 9.0 STATISTICAL CONSIDERATIONS

### 9.1 Study Size Justification

By recruiting 230 participants into Phase I of the study we expect to have complete follow-up data on at least 200. This sample size number is in line with the recommendations from the World Health Organization for clinical evaluation of MC devices, which is based on an ability to rule out an AE rate of about 5% with a new use of a device that has already been shown to be safe in a larger group of men in RCTs and demonstration studies. (WHO 2012)

In Phase II, by recruiting 345 participants, we expect to have complete follow-up data on at least 300. For comparing postoperative pain scores, we will randomize 345 males in 2:1 ratio to topical vs. injectable anesthesia for circumcision. This sample would provide 100% power to detect a mean difference of 1 on the 0 to 10 pain scale using a 2-sided test at the 0.05 significance level. This calculation assumes a standard deviation of 1.8, which is based on prior data. For other binary endpoints, this sample size will provide at least 80% power to detect absolute differences in proportions between groups of at least 20% separately within each site using two-sided tests at the 0.05 significance level. We will not make any adjustments for multiple comparisons between randomized groups.

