All other endpoints will be summarized by anesthetic technique and compared between groups using either two-sample t-tests or chi-squared tests, as appropriate for the endpoint, all conducted at the two-sided 0.05 significance level. We will not make any adjustments for multiple comparisons. 95% confidence intervals for differences between groups will be presented. Missing data will be assumed to be missing in random fashion and ignored.

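### Section 9.2 sends Phase II provider satisfaction to independent-group tests, although the same providers can be expected to assess both anesthetic techniques

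*Combined protocol and SAP*

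**What the plan says.** Section 2.2.2 sets the objective as a comparison: "Compare satisfaction with the topical vs. injectable anesthetic among circumcision providers". Section 3.2.2 gives the method for providers: "we will interview them about their experiences, acceptability and satisfaction with the two anesthetic techniques". Under Phase II in section 8.2, "participants will be randomized to topical or injectable anesthesia in a 2:1 ratio". No section assigns providers to an arm.

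Section 9.2 then sets one rule for everything in Phase II beyond pain and adverse events: "All other endpoints will be summarized by anesthetic technique and compared between groups using either two-sample t-tests or chi-squared tests". The qualifier in "compared between groups using either two-sample t-tests or chi-squared tests, as appropriate for the endpoint" chooses between those two tests and opens no third option. The tests are "all conducted at the two-sided 0.05 significance level", and 95% confidence intervals for group differences are promised. No paired, clustered or descriptive-only method is named for Phase II provider data. Section 9.2 describes itself as a summary and adds: "Any deviations to be made from this summary plan will be documented in the detailed analysis plan".

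**The concern.** A two-sample t-test and a chi-squared test both take the two columns of data as coming from different, independent respondents. Here the respondents on both sides are expected to be the same clinicians. A provider who scores everything generously raises both columns. The two-sample test counts that shared leniency as noise in the comparison, although it cancels when each provider is compared with himself or herself.

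At stake is whether the trial can report fairly what providers think of topical anesthesia, which bears on its uptake. Depending on how the data are collected, the stated rule could hide a real preference behind an over-wide interval, or treat many ratings from a few people as independent opinions.

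**Working it through.** **The plan's own figure.** No power or sample size is stated for provider satisfaction. The nearest figure is the 100% power for pain in section 9.1, where "we will randomize 345 males in 2:1 ratio to topical vs. injectable anesthesia for circumcision", that is 230 vs. 115. With SD 1.8 and a difference of 1, the standard error is 1.8 × √(1/230 + 1/115) = 0.2056, and power is Φ(1/0.2056 − 1.96) = Φ(2.90) = 0.998. With 300 complete (200 vs. 100) it is 0.995. The stated figure reproduces and does not depend on the point made here.

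**Inputs for provider data.** The documents give no number of providers for this trial, no scale, no interview schedule and no correlation. I assume 8, 12 or 21 providers (21 is the count in the earlier ten-site field study, section 1.3.2), a within-provider correlation ρ from −0.3 to 0.7, and a true difference of 0.8 SD for power.

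**Case A: each provider scores both techniques once.** With k providers and common variance σ², the true variance of the mean difference is 2σ²(1 − ρ)/k. The two-sample test uses 2σ²/k. The ratio is 1 − ρ, so in large samples:

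- true size = 2 × [1 − Φ(1.96/√(1 − ρ))]
- interval width relative to the correct one = 1/√(1 − ρ)

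This gives a size of 0.086 at ρ = −0.3, 0.050 at 0, 0.019 at 0.3, 0.0056 at 0.5 and 0.0003 at 0.7. At ρ = 0.5 the interval is 1/√0.5 = 1.41 times too wide.

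Simulation with small numbers (40,000 runs, normal ratings), two-sample / paired t-test:

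| Providers | ρ | Type I error | Power at 0.8 SD |
|---|---|---|---|
| 8 | −0.3 | 0.082 / 0.050 | 0.340 / 0.230 |
| 8 | 0 | 0.047 / 0.049 | 0.318 / 0.281 |
| 8 | 0.5 | 0.011 / 0.050 | 0.277 / 0.496 |
| 12 | 0.5 | 0.008 / 0.049 | 0.460 / 0.715 |
| 21 | 0 | 0.051 / 0.051 | 0.713 / 0.691 |
| 21 | 0.5 | 0.0075 / 0.049 | 0.785 / 0.937 |

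The paired test holds its size throughout. It gains power only under positive correlation. At zero it costs a little, and at −0.3 the two-sample test rejects more often because it is too liberal.

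**Case B: a score is logged after each procedure.** Take 230 vs. 115 ratings spread evenly over k providers, total variance 1, a provider share of 0.05 and a provider-by-technique share s. The provider's general level cancels in the difference, so

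- true variance = 2s/k + (0.95 − s)(1/230 + 1/115)
- variance used by the test ≈ 1/230 + 1/115 = 0.01304

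With s = 0.05 and k = 10: 0.0100 + 0.90 × 0.01304 = 0.02174, a ratio of 1.67, and size 2 × [1 − Φ(1.96/√1.67)] = 0.13. The same formula gives 0.18 for 6 providers and 0.08 for 20. Simulation gave 0.180, 0.123 and 0.083 for 6, 10 and 20 providers, and 0.044 to 0.052 for a test on provider-level differences. With s = 0 the ratio is 0.95 and the size 0.044, so the inflation comes from providers differing in which technique they favor.

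**Yes/no items.** With 21 providers, ρ = 0.5 on the underlying scale, and 85% vs. 50% satisfied, power is 0.748 for chi-squared and 0.681 for exact McNemar. With 12 providers it is 0.458 and 0.227. With 60% satisfied under both techniques, the type I error at 21 providers is 0.017 and 0.016. The exact paired test matches the data structure but does not recover power.

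**The case against.** The best case for the plan has four parts.

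- **The data format is unknown.** Section 3.2.2 promises interviews, not one score per technique, and the data list in section 13.1 has no provider-satisfaction item. Provider opinion in the earlier field study was reported as a single preference (19 of 21, section 1.3.2), and section 3.1.2 lists preference for Phase I. A preference item yields one proportion, to which neither a two-sample nor a paired test of two scores applies. This stands, and the fix has to cover it.
- **The rule may be meant for participants.** Section 9.2 speaks of randomization groups, and one item in section 3.2.2, service optimization, could not be tested this way at all. That reading is reasonable, but the sentence makes no exception and the provider objective is explicitly comparative. The written default is still the wrong test.
- **A detailed plan is to follow.** True, and it is the natural place for the correction. Until a departure is documented there, the summary rule applies.
- **The effect is limited.** No stopping guideline in section 9.3 uses provider satisfaction. This also stands.

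A reader might infer stronger claims that the documents do not support:

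- That power is certain to be lost. This needs positive within-provider correlation, which is plausible but undocumented.
- That per-procedure data hold only as many observations as there are providers. With 10 providers, 23 topical procedures each and a 5% share, the design effect is 1 + 22 × 0.05 = 2.1, leaving about 230/2.1 ≈ 110 effective topical ratings.
- That chi-squared expected counts must fall below 5. This is unavoidable with fewer than 10 providers, but with 20 providers and 70% satisfied the smallest is 20 × 0.30 = 6.

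**Conclusion.** The mismatch is real and small. A stated rule assigns independent-group tests to an endpoint whose two sides are expected to be the same providers. That expectation is a strong inference from the interview wording and from randomization of participants; it is not stated outright.

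If both techniques are scored, the error rate is wrong unless the scores are uncorrelated: conservative under positive correlation and liberal under negative. If scores are logged per procedure, false positives rise to the extent that providers differ in which technique they favor. The named tests suit neither layout in general. The sizes above rest on assumed provider numbers, correlations, effect size and variance shares, so they illustrate direction and order and do not predict this trial. Section 5.0 allows additional clinics, which could raise the number of providers.

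Only one secondary endpoint is touched. I would treat this as a minor correction.

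**What to change.** In section 9.2, or in the detailed analysis plan with the departure recorded, exclude provider-reported endpoints from the general rule and state:

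- The provider is the unit of analysis, and the number of providers is reported as N.
- For graded ratings, each provider's topical minus injectable difference is summarised with a 95% confidence interval and tested with a paired t-test or Wilcoxon signed-rank test. Ratings recorded per procedure are first averaged within provider and technique.
- Yes/no items are shown as a paired two-by-two table and read mainly descriptively, because exact McNemar has low power with few providers.
- A single preference item is reported as a proportion with an exact confidence interval.

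The plan should also say how and when providers are interviewed and on what scale.

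The cost is a few sentences and no new data. The downside is that the visible N becomes the number of providers, which is likely to be small, so the graded ratings and their interval should carry the result.
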